### Sample size and power calculations

Required sample size was calculated to detect a group by time interaction of moderate size (*f* = .21), for 3 groups and 2 time points (T1 and T2). The effect size *f* is defined as *f* = *σ*_*m*_*/σ*, where *σ*_*m*_ is the standard deviation (*SD*) of the effect of interest and *σ* is the common error *SD*. Cohen (1963) suggested that *f* of .25 is a moderate effect. This effect size was chosen because (a) it is a reasonable and achievable statistical effect, and (b) it is substantively and clinically meaningful for the primary outcome measures. The CBCL externalizing subscale score was used in the power calculation because of all the measures in the study (a) it is the one that corresponds most directly to the presenting problem for most participants; and (b) it was used in a previous study conducted at the same site and with a similar study sample, allowing us to obtain realistic estimates of mean CBCL externalizing subscale scores for T1, and for the PCIT-T group at T2. Based on our previous research using a similar sample and the CBCL externalizing subscale as an outcome measure [48], at T1, all groups were assumed to have a mean of 24. Means at T2 were assumed to be 13 (PCIT-T), 16 (COS-P) and 22 (Waitlist). A common SD of 9 and a correlation between measurements of .6 were specified and it was calculated that assuming alpha of .05 and 80% power, a minimum total of 48 participants (i.e. *n* = 16 in each group) would be required. Post hoc testing of differences between the three groups at T2, and a PCIT-T versus COS-P difference at T3, show that *n* = 30 in each group would give 80% power to detect a mean difference between groups of at least 8.0, with *SD* of 9. And alpha of .05/4, to correct for multiple comparisons for all group comparisons at T2 (PCIT-T versus COS-P, PCIT-T versus Waitlist, COS-P versus Waitlist) and T3 (PCIT-T versus COS-P).

## Discussion

Evidence points to the value of parent-child relationship focused interventions for children with early onset attachment and/or behavioral difficulties. Significantly, evidence suggests that interventions that are brief, have a behavioral component, and enhance parental sensitivity are most likely to bring about lasting improvements in children’s attachment security and thus capacity for behavioral and emotional regulation [50]. PCIT-T is a new, innovative early parenting intervention that aligns with these recommendations and is designed to treat families with toddlers who are displaying persistent and significant disruptive behavior difficulties. Like standard PCIT, the program is centered around dyadic parent-child play sessions, with the therapist providing live, in-the-moment feedback and support. PCIT-T aims to increase positive parenting skills (e.g. praise) and sensitivity and decrease use of negative behaviors (e.g. criticism) but there is also a focus on helping parents to better manage their emotions so that they are better placed to help their children manage theirs.

The design of this study has limitations including the different mode of delivery for the two interventions (PCIT-T is delivered individually, COS-P is delivered in a group), the large number of study measures utilized which places burden on participants, and the fact that the waitlist control group will not take part in the 4-month follow-up due to ethical reasons associated with denying patient care for this extended period of time. Finally, while the parent-report measure of child externalizing problems, the CBCL, has been used successfully in previous studies with children aged as young as 12 months [79], it has not been validated for children aged less than 18 months and so there may be issues with the measure for children in the study aged 14–17 months. Despite these limitations, however, the study has a number of strengths including the RCT design, utilization of a clinical sample and a comprehensive mix of parent-report and observational measures.

PCIT-T, delivered in the early toddlerhood period when there is greater plasticity of the developing brain, when capacities for emotional and behavioral control are developing, and when internal representations of attachment relationships are in the critical stages of formation, has the potential to bring about significant and lasting changes for children and families. The current study will evaluate the effectiveness of the most recent iteration of the PCIT-T model [42] and will build on previous pilot studies [45–48] to add to current knowledge about the effectiveness of this new intervention model.

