### Participants and setting

Participants will be 90 toddlers aged 14–24 months with behavioral difficulties referred by a health professional (e.g., General Practitioner (GP), Paediatrician, Early Childhood Nurse, Psychologist) to the Karitane Toddler Clinic (KTC), a specialized outpatient child treatment clinic located in South Western Sydney, Australia. A decision was made to include children aged 14 months and over, rather than the 12 months and over that the PCIT-T intervention is designed for, to increase the likelihood that children in the sample are of a similar developmental stage (e.g., walking, starting to talk) at the time of participation. The study will be advertised using posters and flyers placed in the waiting rooms of GP and Early Childhood Clinics, and online (e.g. advertisements on parenting websites, Facebook and other social media platforms).

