### Procedure

#### Recruitment

After being referred to the KTC, families will be informed about the research study and will undergo a clinical intake procedure including (i) an initial phone-based intake interview conducted by an Intake Officer, (ii) a 20-min in-depth phone-based intake assessment conducted by a member of the clinical research team, and, (iii) for complex cases, case review at a weekly multidisciplinary team meeting. A member of the clinical research team will then phone the families who appear suitable for the KTC service to schedule an initial face-to-face clinical assessment session. To be included in the study, the family must have a child aged 14–24 months, a referral from a health professional, and the parent must give a positive response to one or both of two screening questions (‘Do you have concerns about your child’s behavior?’ and/or ‘Do you have difficulties managing your child’s behavior?’). No other screening questions or measures will be used to assess eligibility, however families will be excluded from the study if there is evidence (in the information obtained in the referral or intake assessment) of severe parental depression with suicidality or other serious mental health conditions causing significant impairment in cognition or behaviors (e.g., psychosis) or if they are not sufficiently proficient in speaking English to complete study measures and protocols. Parents will be told that the study seeks to test different approaches to helping parents who are struggling with challenging toddler behaviour. Eligible and willing parents will provide written, informed consent to participate in the research during the first face-to-face assessment session at the KTC.

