#### Randomization

Participants who meet the study inclusion criteria will be randomly assigned to receive one of the three conditions using restricted block randomization, using block sizes of *n* = 6. This means that within each block of *n* = 6, 2 participants will be allocated to the PCIT-T condition, 2 participants will be allocated to the COS-P condition and 2 participants will be allocated to the Waitlist condition. The order will be randomized within each block. Figure 1 shows the way that participants will flow through the three assessment points for the study (Time 1, T1; Time 2, T2; Time 3; T3). Randomization will occur at the start of the first face-to-face assessment session (T1), with allocations pulled out of pre-prepared sealed envelopes, but the research team and family will not be informed of the condition to which they have been allocated until after completion of the entire T1 assessment.

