Parent-reported *externalizing child behavior* will be assessed using the Child Behavior Checklist for ages 1.5–5 years (CBCL/1.5–5) [78], a validated parent/teacher report scale designed to measure behavioral, emotional and social functioning in children aged 1.5–5 years, and which has been used reliably with children as young as 12 months [46, 79]. The CBCL/1.5–5 comprises 99 items, each rated in terms of the frequency with which the child displays given problem behaviors on a scale of 0–2 (higher scores indicating presence of the behavior). CBCL scores can be summed to yield a ‘total problems’ score and an externalizing sub-scale score can also be computed. In the current study, the parent report version of the CBCL/1.5–5 and the externalizing sub-scale score will be used.

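### CBCL externalizing scores are to be pooled across 18 months, the protocol's own validation limit, with no age term or supportive check in the described analysis

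*Protocol article*

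**What the plan says.** - **Eligibility** (Recruitment): "the family must have a child aged 14–24 months, a referral from a health professional". Under Participants and setting, the lower limit is set at 14 rather than 12 months "to increase the likelihood that children in the sample are of a similar developmental stage".
- **Instrument** (Measures): child externalizing behavior is measured with a checklist designed for ages 1.5–5 years; "the parent report version of the CBCL/1.5–5 and the externalizing sub-scale score will be used". The same paragraph describes it as a scale "which has been used reliably with children as young as 12 months".
- **Admitted limit** (Discussion): "it has not been validated for children aged less than 18 months", and "there may be issues with the measure for children in the study aged 14–17 months".
- **Role of the score** (Sample size and power calculations): the CBCL externalizing score is the basis of the power calculation, chosen as the measure closest to the presenting problem.
- **Allocation** (Randomization): participants are allocated "using restricted block randomization, using block sizes of" six, two per arm. No stratification factor is named.
- **Analysis** (Statistical analysis): linear mixed models with group by time, comparisons of the three groups at T2 and of PCIT-T with COS-P at T3. No age term, age subgroup or age-based sensitivity analysis is named.
- **Another outcome** (Measures): the DECA is given in an infant or a toddler form by age, changing at 18 months. No such distinction is described for the CBCL.

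**The concern.** The protocol raises a question about its sizing measure and then describes an analysis that cannot answer it. If some items fit 14–17-month-olds poorly, their scores carry extra noise, or move with age as well as with treatment. Some children also pass 18 months between T1 and T2, so their change score spans both sides of the validation limit. With no age term, this variation goes into the residual, and a chance difference between arms in the share of younger children goes unadjusted into the contrast. With no analysis at 18 months and over, the report could not say whether the behavior result holds in the age range for which the scale is validated.

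**Working it through.** **1. The plan's own figures.** Inputs from Sample size and power calculations: T1 mean 24; T2 means 13, 16 and 22; SD 9; correlation .6; alpha .05, and .05/4 for pairwise tests. Two-sided tests and no dropout are assumed.

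- Mean changes are −11, −8 and −2, with mean −7 and deviations −4, −1 and 5. Their SD is √(42/3) = 3.74.
- The interaction SD is 3.74/2 = 1.87, so f = 1.87/9 = 0.208 (stated .21).
- SD of change = 9 × √(2 × (1 − .6)) = 8.05. With 16 per group, the noncentral F gives power 0.803.
- Pairwise: 30 per group, difference 8.0, SD 9, alpha .0125. The noncentral t gives power 0.803.

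Both stated figures reproduce, and the sample size is not in dispute here.

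**2. Share under 18 months at each visit.** The age mix is not given. Assume ages uniform from 14 months to either exactly 24 months (10-month span) or the end of the 24th completed month (11-month span). T2 is 8 weeks after T1, 56/30.44 = 1.84 months; T3 is 4 months later.

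| Visit | 10-month span | 11-month span |
|---|---|---|
| T1 | 4/10 = 40% | 4/11 = 36% |
| T2 | (18 − 1.84 − 14)/10 = 22% | 2.16/11 = 20% |
| T3 | 0% | 0% |

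At T3 the youngest child is 14 + 1.84 + 4 = 19.8 months old.

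**3. Chance imbalance at T1.** With K of 90 children under 18 months and three arms of 30, the variance of the difference in counts between two arms is (2/3) × K × (90 − K)/89.

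- K = 36: (2/3) × 36 × 54/89 = 14.6, SD 3.82 children, or 12.7 percentage points.
- K = 33: (2/3) × 33 × 57/89 = 14.1, SD 3.75 children, or 12.5 percentage points.

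A normal approximation with continuity correction for a gap of 6 or more children (20 points), K = 36, has z = 5.5/3.82 = 1.44 and a two-sided probability of about 0.15. Simulating 200,000 random allocations, ignoring the small constraint from blocks of six, gives:

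| Assumed share under 18 months | Given pair | Any pair |
|---|---|---|
| 10% | 1.6% | 3.8% |
| 20% | 7.6% | 17% |
| 36% | 14% | 30% |
| 40% | 15% | 31% |
| 50% | 16% | 33% |

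**4. What such a gap could do to a contrast.** If younger children's scores differ by 1 to 5 points (assumption), a 20-point gap shifts an unadjusted contrast by 0.20 × 1 = 0.2 to 0.20 × 5 = 1.0 CBCL points. The standard error of a two-arm difference is 9 × √(2/30) = 2.3. The PCIT-T versus COS-P difference assumed at T2 is 16 − 13 = 3.

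**5. What an analysis at 18 months and over can deliver** (SD 9, alpha .0125, difference 8.0).

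| Share excluded | Left per arm | Pairwise power | Detectable at 80% |
|---|---|---|---|
| 20% | 24 | 68% | 9.0 |
| 36% | 19 | 55% | 10.2 |
| 40% | 18 | 52% | 10.5 |

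Power for the group by time interaction stays at 85–87% with 18–19 per arm.

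**The case against.** The protocol does not hide the point. It lists it as a limitation and cites reliable use from 12 months. Reliable use and lack of formal validation are compatible, so Measures and Discussion do not contradict each other. Randomization balances age in expectation, and the error rate of the test already allows for chance imbalance. A shift of 0.2–1.0 points is small beside a standard error of 2.3. The group by time test also removes age differences that are constant over time. Finally, a covariate or sensitivity analysis may stand in an analysis plan that is not shown.

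Most of this stands, and it rules out some stronger readings:

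- A reader might infer that a third or more of the behavior result rests on an unvalidated score. That share is a T1 figure under an assumed age mix. The planned group comparisons are at T2, where it is about a fifth, and at T3, where it is zero.
- A reader might take the younger children's scores to be invalid. The protocol says only that the scale is not validated there and that problems are possible.
- A reader might see unstratified allocation as an error or a source of bias. It is neither. Stratifying by age is optional in a trial of 90 families.
- A reader might treat the CBCL as the sole primary outcome. It drives the sizing, but it is one of 14 rows in Table 1 and is not singled out as primary.

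What remains is that disclosure does not test the matter. The subtraction of constant age differences does not help if change itself differs with age, or for a direct contrast at T2. Since the analysis plan is not shown, the point is put as an addition to the model that the article states, not as proof that nothing exists elsewhere.

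**Conclusion.** The concern holds in a limited form. The protocol admits an age band for which it says its sizing measure is not validated, and the analysis it describes pools across that boundary without an age term or a check. Under uniform ages, the band covers about 36–40% of children at T1, 20–22% at T2 and none at T3. A gap of 20 points or more between arms then has a chance of about 15% for a given pair and 30% for any pair; with a 20% share these fall to about 8% and 17%. The consequences are lost precision, chance imbalance and a result that is harder to interpret, not systematic bias. How far scores under 18 months actually misbehave cannot be known from the article.

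**What to change.** 1. In Statistical analysis, add age at T1 as a covariate in the linear mixed models and, for the CBCL externalizing score, an age by time term. Age is already known from eligibility. The cost is one parameter per model and, with three visits, two more for the CBCL.
2. Pre-specify a supportive analysis of the CBCL externalizing comparison in children aged 18 months or more at T1. Report the estimate with its confidence interval beside the whole-sample result. Do not make the whole-sample claim depend on it: with about 18–19 per arm under the uniform assumption, a disagreement could easily be chance.
3. Report the number and share of children under 18 months by arm at each visit, which replaces the assumption used here with data.

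None of this changes who is enrolled, the treatments or the sample size. Separate sealed envelopes for 14–17 and 18–24 months are an option for children not yet allocated. Changing allocation partway through has drawbacks of its own, and the three steps above do not depend on it.

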## Data Availability

Not applicable.

## Abbreviations

ABC: Attachment and Biobehavioral Catchup
AQS: Attachment Q-Sort
BCAP: Brief Child Abuse Potential Inventory
CBCL/1.5–5: Child Behavior Checklist for ages 1.5–5 years
COS-I: Circle of Security Intensive Intervention
COS-P: Circle of Security – Parenting™
CDI-T: Child Directed Interaction – Toddlers
CHQ: Caregiving Helplessness Questionnaire
CTNES: Coping with Toddler’s Negative Emotions Scale
DECA: Devereux Early Childhood Assessment
DECA-I: Devereux Early Childhood Assessment - infant version
DECA-T: Devereux Early Childhood Assessment - toddler version
DERS: Difficulties in Emotion Regulation Scale
DPCIS-IV: Dyadic Parent-Child Interaction Coding System, Fourth Edition
GP: General Practitioner
ITT: Intention-to-treat analyses
KTC: Karitane Toddler Clinic
NICHD-SECCYD: NICHD Study of Early Child Care and Youth Development: Sensitivity Scales
PCIT: Parent Child Interaction Therapy
PCIT-T: Parent Child Interaction Therapy – Toddler
PDI-T: Parent Directed Interaction-Toddlers
PSI-SF: Parenting Stress Index–Short Form
SSP: Strange Situation Procedure
RCT: Randomized Controlled Trial
T1: Time 1
T2: Time 2
T3: Time 3
VIPP-SD: Video-feedback Intervention to promote Positive Parenting and Sensitive Discipline
